#### Secondary Measures

*GERD-HRQL:* The GERD-HRQL questionnaire is a validated 11 item scale for assessing the impact of GERD symptoms on HRQL (24).

*Nepean Dyspepsia Index:* The Nepean Dyspepsia Index is a validated 10 item scale for measuring dyspepsia-specific HRQL in 5 domains (25).

*SF-12:* The SF-12 is a validated 12 item questionnaire for measuring overall HRQL in 6 domains (26).

*MYMOP:* The Measure Yourself Medical Outcome Profile (MYMOP) is a validated 7 item measure of the impact of treatment on symptom severity and overall well-being (27). It has been used in a variety of studies of CAM and conventional modalities.

*Treatment satisfaction:* A 4 question assessment of satisfaction with GERD treatment (28).

#### Other Measures

*Study diary:* Changes in non-GERD, non-dyspeptic symptoms will be assessed by reviewing the study diaries and the MYMOP questionnaire.

*Study diary:* Study drug and rescue medication use will be assessed by reviewing the study diaries.

*Medications and supplement questionnaire:* All subjects will complete a medication and supplement use questionnaire at their first and second study visits to determine if there have been any medication or supplement changes during the study period. The questionnaire will be reviewed by the study physician with the subject.

*GSRS:* The Gastrointestinal Symptom Rating Scale is a validated 15 item instrument for measuring the severity of gastrointestinal symptoms (23). It contains 5 subscales: abdominal pain, reflux syndrome, diarrhea syndrome, indigestion syndrome, and constipation syndrome.

*Credibility questionnaire:* To assess how subjects' views regarding the study treatment change over time, we will have subjects complete the Borkovec and Nau credibility questionnaire (29) before and after the clinical interview and at the 2 week follow-up visit.

*CARE:* To assess subjects' perceptions of their intake with the study physicians, they will complete the Consultation And Relational Empathy questionnaire (30), a validated 10 item measure for assessing the quality of the patient encounter and perceptions of empathy from the treatment provider.

*CAMBI:* To assess subjects' beliefs and expectations regarding complementary medicine, we will have them complete the Complementary and Alternative Medicine Beliefs Inventory, a validated 17 item questionnaire (31).

*Treatment assignment:* At the second study visit, we will ask participants whether they think they were assigned to the Acidil or placebo groups and how certain they are of this belief.

*Belief in homeopathy:* We will ask subjects 2 questions about their use of, and belief in, homeopathy during the second visit to better understand perceptions regarding this treatment modality in this population.

*Interview:* We will conduct a semi-structured interview to assess subjects' experiences with the trial for qualitative analysis.

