During the consent process, we will not inform study subjects of the name of the study supplement or that it is a homeopathic product. Acidil is widely available over the counter, inexpensive (less than \$10 for 60 tablets), and we are unable to obtain a placebo that is an exact match for the product. As such, it would be very easy for subjects to unblind themselves during the trial and invalidate the results of the study. Furthermore, it is likely that most of the lay public do not know exactly what homeopathy is, and if they were to read the word “homeopathy” or “Acidil” in the consent document, they would likely search the internet or seek out additional information after the first study visit. Beliefs and expectations are known to influence treatment responses, and we are interested in studying how the length of time and depth of questions asked during a physician interview affects patients’ beliefs about the effectiveness of a treatment. Given the controversy surrounding homeopathy and the variable quality of information on the internet, subjects’ beliefs about the treatment would likely change and could weaken the difference between the effect of the standard vs. expanded interviews. Finally, many people would argue that calling Acidil “homeopathy” is also deceptive as classical homeopathy relies on the prescription of a single homeopathic medicine at higher dilutions closer to, or beyond, Avogadro’s number. The product being studied contains a combination of homeopathic medicines at relatively low dilutions (i.e., more concentrated than typical homeopathic medicines), and thus is more like a supplement than traditional homeopathy. We believe that the way we have described this product in the consent (a combination of 4 plant-based products, each in a low dose) is the best way to describe the intervention while maintaining the validity of the study. After the exit interview subjects will be informed of the name of the study supplement (Appendix F). However, because of the need to maintain the study physician’s blinding, they will not be informed whether they received Acidil or placebo until after the trial is over via a letter (Appendix F).

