#### Second Study Visit (Time 2 - approximately 2 weeks after first visit):

Study diaries will be collected and subjects will provide a second blood specimen (if they consent to the repository study) and complete study questionnaires (medication and supplement use, GSRS, Nepean Dyspepsia Index, GERD-HRQL, SF-12, MYMOP, treatment satisfaction, credibility questionnaire, predicted treatment assignment, belief in homeopathy, see Table 1). Subjects will then have a brief semi-structured exit interview with the study physician or another member of the research team (Appendix D) inquiring about their use of the study medication, symptoms, and experience in the trial. After the interview, subjects will be debriefed regarding the concealment of the doctor-patient interaction study in this trial and will be informed of the name of the study supplement (Appendix F). The second study visit is anticipated to last approximately 1 hour. Subjects who continue to experience symptoms at the end of the trial will be referred to their PCP for further evaluation.

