#### Phone calls:

When subjects call indicating an interest in participating in the study, we will attempt to call them

back up to 5 times. If the potential subject does not answer or return calls, no further attempts to contact that individual will be made.

If a subject is unable to attend, or misses, the second clinic visit, we will attempt to contact the subject up to 5 times to reschedule and/or complete the follow-up study questionnaires by phone and/or mail.

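### As described, the visit 2 questionnaires name Acidil and raise homeopathy before the point at which the protocol plans to tell subjects the product's name

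*Protocol*

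**What the plan says.** The section Acidil and Placebo Groups sets out the concealment: "During the consent process, we will not inform study subjects of the name of the study supplement or that it is a homeopathic product". One reason given is that the product is cheap and on open sale and the placebo is not an exact match, so that "it would be very easy for subjects to unblind themselves during the trial and invalidate the results of the study". The same section fixes when the name is released: "After the exit interview subjects will be informed of the name of the study supplement (Appendix F").

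The Second Study Visit section lists the questionnaires, ending with "treatment satisfaction, credibility questionnaire, predicted treatment assignment, belief in homeopathy, see Table 1". The interview comes next: "Subjects will then have a brief semi-structured exit interview with the study physician or another member of the research team". The debriefing, at which the name is given, follows the interview.

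Other Measures describes the treatment-guess item: "we will ask participants whether they think they were assigned to the Acidil or placebo groups". It also adds two visit 2 questions on use of, and belief in, homeopathy.

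For subjects who cannot attend or who miss visit 2, the Phone calls section allows them to "complete the follow-up study questionnaires by phone and/or mail". Physical Setting (B7) likewise allows the second questionnaire set to be done from home or by telephone.

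**The concern.** The protocol argues that reading either the product name or the word homeopathy would probably send subjects looking for information and change their beliefs. Yet both words appear in its description of items that subjects answer before the planned disclosure.

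Three things are at stake:

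- **The guess.** It is the only listed measure of subject blinding. Subjects were told about a low-dose combination of four plant-based products, so an unfamiliar brand name in the question could affect the answer.
- **The exit interview.** It is kept for qualitative analysis and follows both cues.
- **The other week-2 questionnaires.** Quality of life is analysed under Hypotheses 2c and 3b. MYMOP, satisfaction and credibility are exploratory analyses 5, 6 and 8. These are exposed only if a subject can see the cues before answering them.

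**Working it through.** No arithmetic applies. The check sets the sections side by side and follows the order of events.

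**1. In-person visit 2, in the order given under Second Study Visit**

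| Step | Content | Cue already met? |
|---|---|---|
| 1 | Diaries collected | No |
| 2 | GSRS, Nepean Dyspepsia Index, GERD-HRQL, SF-12, MYMOP, satisfaction, credibility | No |
| 3 | Predicted treatment assignment | Product name, if worded as Other Measures describes |
| 4 | Belief in homeopathy | Name, then the topic of homeopathy |
| 5 | Exit interview | Both |
| 6 | Debriefing, name disclosed | Planned disclosure point |

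Steps 3 and 4 come before step 6, so the literal description in Other Measures conflicts with the disclosure point. The Study Measures and Timepoints table runs in a compatible order: satisfaction is row 10, credibility row 11, the guess row 14, homeopathy row 15 and the interview row 16.

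**2. What the cues can reach in person.** If the listed order is followed, they reach the guess, the homeopathy answers and the exit interview. They do not reach:

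- the diary outcomes, because the diaries are listed as collected first;
- the belief measures for Hypothesis 3c, because that analysis uses pre-treatment CAM belief and credibility scores. CAMBI is completed before the clinical interview at visit 1, and credibility is measured before and after that interview.

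**3. What the cues can reach by mail or at home.** Neither Phone calls nor Physical Setting states an order of forms, says whether all forms go out together, or requires the diary back first. If all forms arrive together, a subject could read steps 3 and 4 before completing step 2. That subject could also search the name, or compare the tablets with a retail product that the protocol prices at under $10 for 60. This is the self-unblinding route that the concealment was meant to close.

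**4. What the items disclose.** The guess item, as described, gives a name but not the allocation. The homeopathy questions, as the measures table describes them, ask whether the subject has heard of homeopathy and what they think of it. They suggest what the product is without saying so.

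**5. How many subjects.** Every in-person subject would meet the cues before the exit interview. The number of remote completions is not given. The target of more than 90% completion does not bound it, because it does not separate attended from remote completion.

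**The case against.** The strongest objection is that the form itself cannot be seen. The instruments are in Appendix D, which is not at hand. Other Measures is written for investigators, and the protocol uses Acidil or placebo as its arm label elsewhere, including where it describes handing medication to subjects who are not told the name. The measures table describes the same item without the name. The word may therefore never reach a subject. This stands as a limit on what can be claimed, but the protocol text still needs reconciling with its own disclosure point.

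Second, a sensible order is already listed, with the guess and homeopathy items after the other questionnaires. This stands for in-person visits, although a list is not a rule of administration. It gives no protection for mailed forms.

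Third, concealment was meant to protect the trial period, which is essentially over at visit 2. This also largely stands in person. It is weaker for remote completion, where nothing says the diary is returned before the forms are read.

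Fourth, mail is a contingency, with rescheduling and telephone as alternatives, and none of the analyses listed in the protocol uses the guess. Both points are fair and keep the matter small.

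A reader might infer that treatment blinding is broken, or that the belief mechanism under Aim 3 is compromised. The documents support neither. No item reveals the arm, and Hypothesis 3c rests on beliefs measured before treatment. A reader might also infer that the product's homeopathic nature has its own scheduled disclosure. The protocol sets a time only for the name.

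**Conclusion.** The point holds as a minor internal conflict. The guess item as described, and the visit 2 sequence, do not fit the protocol's plan to release the name only after the exit interview.

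In person, the reach is limited to the guess, the homeopathy answers and the exit interview, provided the listed order is followed. In mail or home completion, it could extend to the week-2 quality-of-life, MYMOP, satisfaction and credibility scores, because no order is set.

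The part about the name assumes that the form is worded as Other Measures describes. The remote part assumes that forms can be read together. The documents do not allow any estimate of how many answers would change, so no size of bias is claimed. It would be too strong to conclude that the efficacy results are invalidated: in person, the chief efficacy outcome comes from diaries listed as collected before either cue.

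**What to change.** 1. Check the guess item in Appendix D. In both the form and Other Measures, word it as a choice between the study supplement and placebo, which matches what subjects were told.
2. State that the guess is completed after the symptom, quality-of-life, satisfaction and credibility forms.
3. Move the two homeopathy questions to after the exit interview, immediately before the debriefing.
4. For mail or telephone follow-up, ask the guess and homeopathy items only once the diary and the other forms have been returned or completed.

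Items 1 to 3 cost a wording change and a re-ordering, with no added measure. Item 4 costs one short extra contact for each mailed case.

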#### Phone calls:

When subjects call indicating an interest in participating in the study, we will attempt to call them

back up to 5 times. If the potential subject does not answer or return calls, no further attempts to contact that individual will be made.

If a subject is unable to attend, or misses, the second clinic visit, we will attempt to contact the subject up to 5 times to reschedule and/or complete the follow-up study questionnaires by phone and/or mail.

#### Monitoring of Adverse Events and Patient Safety:

Any and all adverse events will be reported to our independent safety and monitoring board. No interim analyses of study efficacy are planned due to the pilot nature of this study.

## **B. Statistical Considerations**

### **Sample Size Justification:**

We will screen a sufficient number of subjects to consent/enroll 24 subjects total into the study, 6 subjects in each of the 4 groups. This number was determined to ensure that we can complete enrollment within a 6-12 month time frame to assess study feasibility as our primary outcome.

As this is a pilot feasibility study, we do not anticipate having adequate power to show significant differences in treatment effects between groups, but do hope to generate estimates of effect sizes and demonstrate trends. Our chief secondary outcome will be the percent of subjects with 50% or greater improvement in heartburn symptom severity for the last 7 days of the study compared to baseline (compare groups 1+3 vs. groups 2+4 [Aim 2a] and groups 1+2 vs. groups 3+4 [Aim 3a]). We will also assess the percent of subjects with dynamic changes in heartburn symptom severity during the study period compared to baseline (compare groups 1+3 vs. groups 2+4 [Aim 2b]).

Table 2 illustrates power estimates using the Fisher exact test for between group differences ranging from 0.25 – 0.4 for an alpha of 0.05 and sample sizes of 24 subjects and 20 subjects per group (combining groups 1+3 and 2+4 or groups 1+2 and 3+4 for all analyses). We anticipate that we will have 30-50% power to detect a difference between groups. These power calculations are based on the assumption of no interaction effect.

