### B3. DESCRIPTION OF RESEARCH PROTOCOL

#### A. Study Design – Overview, Methods, Procedures

##### Overview

We propose to conduct a single-center, pilot feasibility, 2x2 factorial design randomized controlled trial assessing the effect of a homeopathic supplement (Acidil) and components of the placebo response (doctor-patient interaction and beliefs/expectations) on symptoms and HRQL in patients with GERD over a 2 week time interval. The Acidil vs. placebo intervention will be double-blinded and the standard vs. expanded interview intervention (doctor-patient interaction) will be single-blinded. Randomization will be by permuted block randomization with block sizes of 4 and 8. We plan to enroll 6 patients into each group for a total of 24 subjects in the study according to the adjacent scheme. Subjects will be evaluated in the GCRC at BIDMC at two timepoints: baseline and at 2 week follow-up.

|                    | Acidil  | Placebo |
|--------------------|---------|---------|
| Standard Interview | Group 1 | Group 2 |
| Expanded Interview | Group 3 | Group 4 |

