**Table 2: Power Estimates.**

| p1* | p2* | Difference | Power, n=24 | Power n=20 |
|------------|------------|-------------------|--------------------|-------------------|
| .25        | .5         | .25               | .325               | .261              |
| .35        | .6         | .25               | .307               | .247              |
| .45        | .7         | .25               | .313               | .252              |
| .2         | .5         | .3                | .479               | .391              |
| .3         | .6         | .3                | .445               | .362              |
| .25        | .6         | .35               | .595               | .497              |
| .35        | .7         | .35               | .585               | .488              |
| .2         | .6         | .4                | .740               | .640              |
| .3         | .7         | .4                | .719               | .619              |

\*p1 and p2 are the proportion of subjects in comparison 1 vs. comparison 2.

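### Table 2 and the 30-50% power statement count 24 and 20 subjects on each side of a comparison, but a 24-subject trial has 12 per side, so the stated power is about double the real figure

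*Protocol*

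**What the plan says.** The Overview of the study design says "We plan to enroll 6 patients into each group for a total of 24 subjects in the study". The Sample Size Justification repeats the number: the team will "consent/enroll 24 subjects total into the study, 6 subjects in each of the 4 groups". The chief secondary outcome is the proportion of subjects whose heartburn severity improves by at least 50%. It is analysed by pooling cells across the other factor: "compare groups 1+3 vs. groups 2+4 [Aim 2a] and groups 1+2 vs. groups 3+4 [Aim 3a".

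The same section then introduces Table 2 as "power estimates using the Fisher exact test for between group differences ranging from 0.25 – 0.4 for an alpha of 0.05", with "sample sizes of 24 subjects and 20 subjects per group (combining groups 1+3 and 2+4 or groups 1+2 and 3+4 for all analyses". The table has one column for n=24 (power .307 to .740) and one for n=20 (.247 to .640). Its footnote says only that "p1 and p2 are the proportion of subjects in comparison 1 vs. comparison 2". The text concludes: "We anticipate that we will have 30-50% power to detect a difference between groups". It adds: "These power calculations are based on the assumption of no interaction effect".

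**The concern.** The wording that introduces Table 2 defines a group as two cells pooled, and gives that pooled group 24 or 20 subjects. The whole trial has only 24. If the table was really calculated that way, its power figures belong to a trial of twice the planned size, and so does the power statement drawn from it.

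What is at stake is how the results will be read. The protocol hopes to show trends and to supply effect sizes for a larger trial. A reader told that a 0.40 difference had 72-74% power would treat a null result as fairly informative. If the true figure is near 39%, it is not.

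The label n=24 could also be a slip for the total, with the arithmetic done correctly at 12 per side. The printed values can settle that.

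**Working it through.** **Inputs**
- Total 24, four cells of 6 (Overview; Sample Size Justification).
- Comparisons 1+3 vs 2+4 and 1+2 vs 3+4, so each side has 6 + 6 = 12.
- Fisher exact test, alpha 0.05 (Sample Size Justification). Sidedness is not stated; both were tried.
- Nine pairs p1, p2 and the printed power (Table 2).

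**Trial size implied by the wording.** 24 per pooled side needs 2 × 24 = 48 subjects; 20 per side needs 2 × 20 = 40.

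**Formula.** For n subjects per side, with b the binomial probability,

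Power = Σₓ Σᵧ b(x; n, p1) · b(y; n, p2) · 1[Fisher p(x, y) ≤ 0.05], with x and y each running from 0 to n.

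**Step 1: reproduce Table 2 (two-sided)**

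| p1 | p2 | Table 2, n=24 | Exact, 24 per side | Table 2, n=20 | Exact, 20 per side |
|---|---|---|---|---|---|
| .25 | .50 | .325 | .337 | .261 | .269 |
| .35 | .60 | .307 | .331 | .247 | .230 |
| .45 | .70 | .313 | .332 | .252 | .245 |
| .20 | .50 | .479 | .493 | .391 | .409 |
| .30 | .60 | .445 | .471 | .362 | .347 |
| .25 | .60 | .595 | .620 | .497 | .493 |
| .35 | .70 | .585 | .616 | .488 | .468 |
| .20 | .60 | .740 | .760 | .640 | .650 |
| .30 | .70 | .719 | .750 | .619 | .599 |

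The largest gap is 0.031 in the n=24 column and about 0.02 in the n=20 column. The usual continuity-corrected approximation replaces n by n(1 − 1/(n·d))², where d is the difference. For .25 vs .50 at 24 per side this is 24 × (1 − 1/6)² = 16.7, giving power .314 against the printed .325. All 18 cells agree with this method to within 0.016.

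**Step 2: test the reading that n=24 is the total.** At 12 per side, exact two-sided Fisher gives .143 for the first row, against .325. Uncorrected chi-square, arcsine and one-sided versions do not rescue it. One of the closest, one-sided uncorrected chi-square, gives .347 for .25 vs .50 but .651 for .20 vs .60, where the table prints .740. One-sided calculations at 24 per side are too high throughout (exact Fisher .446 to .844). The table was therefore computed with 24 and 20 on each side.

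**Step 3: power of the planned trial (exact, two-sided)**

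| p1 | p2 | Difference | 12 per side | 11 per side | 10 per side | Table 2 (n=24) ÷ 12 per side |
|---|---|---|---|---|---|---|
| .25 | .50 | .25 | .143 | .112 | .086 | 2.27 |
| .35 | .60 | .25 | .146 | .112 | .083 | 2.10 |
| .45 | .70 | .25 | .144 | .112 | .083 | 2.17 |
| .20 | .50 | .30 | .210 | .169 | .132 | 2.28 |
| .30 | .60 | .30 | .211 | .165 | .123 | 2.11 |
| .25 | .60 | .35 | .292 | .233 | .179 | 2.04 |
| .35 | .70 | .35 | .293 | .232 | .176 | 2.00 |
| .20 | .60 | .40 | .392 | .321 | .253 | 1.89 |
| .30 | .70 | .40 | .389 | .316 | .243 | 1.85 |

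Only the two 0.40 rows exceed 30% at 12 per side. Eleven per side corresponds to the protocol's retention target: 0.90 × 24 = 21.6, so 22 completers. Ten per side is 20 completers, 20/24 = 83% retention.

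**Step 4: precision.** The 95% half-width for a risk difference is 1.96 × √{[p1(1 − p1) + p2(1 − p2)]/12}. For .20 vs .60 it is 1.96 × √(.40/12) = 0.36; for .35 vs .60 it is 1.96 × √(.4675/12) = 0.39. The other rows lie between. The interval is about as wide on each side as the largest differences in the table.

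**The case against.** The strongest reply is that nothing rests on Table 2. The protocol says the sample size follows from what can be enrolled in 6-12 months, makes feasibility the primary outcome, and states that it does not expect adequate power. Correcting the table moves an admittedly underpowered comparison to a more underpowered one. This stands as a limit on the consequences: no sample size, endpoint, test or decision rule changes. It does not rescue the figures. The protocol chose to quantify its power, and a general caveat does not correct numbers that are wrong by a factor of two.

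Three narrower points also have weight.
- The 30-50% sentence is not clearly at odds with the table's own range. For differences of 0.25 to 0.30 the n=24 column runs from .307 to .479, which the sentence may be summarising. Its fault is the wrong n; it also does not say which differences it covers.
- The corrected values are still Fisher power under no interaction, whereas the Data Analysis section plans logistic regression with an interaction term. They are a like-for-like correction of Table 2, not the power of the planned model.
- Ten per side falls short of the protocol's own target of more than 90% retention, so the 8% floor is a pessimistic case. The protocol's second, smaller-n column makes showing such a case reasonable.

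**Conclusion.** The error is real and lies within the Sample Size Justification. The trial gives 12 subjects per side; Table 2 was calculated for 24 and 20 per side. At the planned size, power for differences of 0.25 to 0.40 is about 14-39%, against a printed 31-74% in the n=24 column. It falls to 11-32% with 11 per side and 8-25% with 10. The statement of 30-50% power is untrue for seven of the nine scenarios before any dropout.

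These figures assume 1:1 pooled sides, exact two-sided Fisher at alpha 0.05 and no interaction. Two-sidedness is inferred, because only two-sided values match the table. With the continuity-corrected approximation the overstatement is somewhat larger, 2.2 to 2.6 times. The document does not show how the doubling arose, and the conclusion does not depend on it.

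**What to change.** - Recompute Table 2 at 12 per side, with 11 and 10 per side as dropout cases, and label each column as the number per side of the pooled comparison. State that the test is two-sided.
- Replace the 30-50% statement with about 14-39% power for differences of 0.25 to 0.40 without dropout (11-32% with 11 per side, 8-25% with 10), and name the differences it refers to.
- Optionally, add the expected precision for the responder difference: a 95% half-width of roughly 0.36 to 0.39 with 12 per side. This suits the stated purpose of estimating effect sizes better than power does.

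The cost is one recalculated table and one or two sentences. No subjects, procedures or analyses change; the stated power simply becomes less favourable.
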